#### Statistical analysis

A series of 3 (condition: control, intervention, and intervention with text message) × 2 (time: 6 and 12 weeks) mixed model multivariate analyses of covariance (MANCOVAs) with time as a repeated measures variable will be used examine the effects of the intention over time on study outcome variables. Baseline measures will be covariates in the model. A separate MANCOVA will be conducted for each set of dependent outcome variables: biomedical, behavioural and psychological. Pending significant multivariate effects, follow-up univariate analysis of covariance (ANCOVAs) will be used to identify differences for individual variables within each outcome set. Post-hoc follow-up tests will also be conducted to locate individual differences at the time intervals. Mediation analyses will be conducted by mediated multiple linear regression analysis with dummy-coded intervention conditions as the independent predictor variables, the constructs from the HAPA included as mediating variables, and the primary and secondary biomedical outcome variables as the dependent variables. Mediation will be confirmed through significant bootstrapped indirect effects using Preacher and Hayes’ [56] algorithms for multiple mediation and the PROCESS macro. Missing data will be handled by multiple imputation using regression analysis with the Markov-chain Monte Carlo (MCMC) estimation method. In addition, we will adopt a full intention-to-treat analysis with last measured data points carried forward in order to provide a conservative estimate of the effects.

Sample size has been determined by a power analysis using the G*Power 3.1 Program, suitable to evaluate differences between the three condition levels greater than 10%, with statistical power set at > 0.80 and alpha set at *p* < .05 [57]. A large effect size is assumed as previous studies that have used implementation intentions and reminder text messages [31], as well as studies using mental imagery and implementation intentions to increase exercise behaviour [58], have found large effect sizes. Given the estimated effect size, the total sample size required post-test is 66 and considering a potential 35% drop out rate and eliminations of cases due to missing data or spoilt questionnaires based on previous trials [21], we plan to recruit 102 participants at baseline or until the required sample size has been achieved.

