### Hypotheses

The main hypothesis is that the intervention conditions adopting implementation intentions and mental imagery techniques, will result in statistically-significant independent improvements in the outcome measures relative to the control condition from the time of intervention and at 6 and 12 weeks. We also expect statistically-significant differences in the outcome variables across the two intervention conditions, such that the intervention condition with text messages leads to greater weight loss that the intervention condition alone.

It is also hypothesised that relative to baseline and week 6 and 12, the intervention with text message condition will lead to statistically-significant independent improvements on the biomedical, psychological, and behavioural outcome measures, compared with the intervention and control conditions. In particular, we expect to find statistically-significant differences in the key HAPA-based psychological mediators of the effects of the intervention components including planning (relevant to implementation intentions) and self-efficacy and motivation (relevant to mental imagery) over the same follow-up time points.

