Participants will need to provide written consent prior to participation. Prior to each clinic appointment participants will complete questionnaires measuring baseline psychological and behavioural outcomes including a 3 day food, drink, and exercise diary. Within a three day period, prior to their clinic appointment, participants will be required to attend to a pathology clinic to take blood sample measures. Furthermore, at each clinic appointment participants will engage in baseline biomedical assessments: blood pressure, weight, waist-hip ratio, and at baseline and week 12 body composition measures. At the first clinic appointment participants will be asked to view a pre-recorded video presentation that contains the intervention information, followed by the completion of a questionnaire containing the post-intervention measures. One of two video presentations will be provided to participants, one designed for the control condition participants, and the other for the two intervention conditions. The duration of the video presentation is approximately 60 and 76 minutes for the control and intervention conditions respectively. Due to the pauses in the video to complete various activities and the break time the intervention manipulation duration may last approximately 90 to 120 for the control condition, and 150 to 210 for the intervention conditions. In addition, participants allocated to the intervention with text message condition will receive goal reminder text messages over the 12 weeks of the intervention. Prior to leaving the clinic, all participants will be provided with their future appointment times and a set of tools to assist them with monitoring their physical activity and calorie intake: A copy of the Calorie King™ book [36], Calorie Counter diary [37], the Australian dietary guidelines [38], and Australian physical activity guidelines [39]. Participants will be encouraged to contact the researcher if any queries arise. In addition, a personalised email providing a handout of the essential program information such as the guidelines and the participant’s responses to various activities (including goals) when watching the video presentation will be sent to the participant via email. The participant responses to the activities will be assessed by the research team to ensure program compliance.

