### Psychological measures

Participants will be instructed to complete the outlined psychological measures before and after viewing the video presentation intervention unless specified otherwise. Variables from the HAPA will be measured to assess the psychological mediators that may explain the effects of the intervention on the behavioural and biomedical outcomes. The HAPA measures include items adapted from Barg and colleagues’ [51] measure of assessing risk perception for developing cancer for physically inactive middle aged adults. *Risk perception* will be assessed using four items on a 6 point Likert scale ranging from 1 (strongly disagree, much lower, not likely) to 6 (don’t know/refused) to measure perceived risk of developing obesity related risk factors. For example, “I think it is likely that I will develop health problems related to obesity at some point in my life.” *Outcome expectancy* will be assessed using six items with responses ranging from 1 (strongly disagree, not at all effective) to 5 (strongly agree, extremely effective) to question participants about the effect of diet and physical activity on health risks related to weight gain. For example, “I think that consuming fewer calories per day is a very important way to help me to lose weight”. *Intention* will be assessed with four items that ask participants how much they plan and intend to follow the diet guidelines and/or to participate in the recommended physical activity amount over the next 12 weeks. Responses range from 1 (strongly disagree) to 5 (strongly agree). For example, “I intend to participate in daily physical activity with a minimum of 30 minutes of planned exercise on each individual occasion over the next 6 weeks. *Action self-efficacy* will be measured using 10 items regarding participants’ confidence and ability to engage in the recommended diet and physical activity guidelines over the next 12 weeks. Prior to answering the questions, participants would have heard the recommendations during the video presentation. Items are on a 5 point Likert scale ranging from 1 (not confident, not likely, strongly disagree) to 5 (completely confident, extremely confident, strongly agree). For example, “if it were entirely up to you, how confident are you that you would be able to follow a diet that requires you to consume fewer calories per day on each individual occasion over the next 6 weeks?” *Maintenance self-efficacy* will be measured using 18 items on a 5 point Likert scale ranging from 1 (not confident) to 5 (completely confident) to measure barriers to engage in the recommended physical activity or diet guidelines. For example, participants were asked “How confident are you that you will do daily physical activity with a minimum of 30 minutes of planned exercise during your leisure time on each individual occasion over the next 6 weeks even if…” followed by a list of barriers, such as, but not limited to bad weather and feeling tired. The participants *planning* will be assessed using two items ranging from 1 (strongly disagree) to 5 (strongly agree) that ask participants if they had made a detailed plan about when, where and how they would engage in physical activity or follow the diet guidelines. For example, “I have made a detailed plan about when, where, and how I will do daily physical activity with a minimum of 30 minutes of planned exercise on each individual occasion over the next 6 weeks”.

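### Psychological scores taken straight after the video have no stated role in the analysis, and the carry-forward rule, read literally, would use them as week-6 and week-12 values

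*Protocol article*

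**What the plan says.** All of this is in the protocol article.

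- **Procedure.** At the first clinic appointment participants watch the video, "followed by the completion of a questionnaire containing the post-intervention measures".
- **Psychological measures.** Participants "complete the outlined psychological measures before and after viewing the video presentation intervention", unless a scale is described otherwise. Two scales differ. Motivation is placed at baseline. Action self-efficacy is described as answered by people who have already heard the video's recommendations.
- **Hypotheses.** The main hypothesis is improvement "relative to the control condition from the time of intervention and at 6 and 12 weeks".
- **Statistical analysis.** The between-arm tests are three conditions by two times: "time: 6 and 12 weeks) mixed model multivariate analyses of covariance (MANCOVAs) with time as a repeated measures variable". "Baseline measures will be covariates in the model". "A separate MANCOVA will be conducted for each set of dependent outcome variables: biomedical, behavioural and psychological". The follow-up ANCOVAs and post-hoc tests derive from these models.
- **Statistical analysis, mediation.** Regressions use condition dummies as predictors, HAPA constructs as mediators and biomedical variables as outcomes. The time at which the mediators are taken is not given.
- **Statistical analysis, missing data.** Multiple imputation is planned. In addition there is an intention-to-treat analysis that carries each participant's last value forward, which the article presents as conservative.

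**The concern.** A scheduled assessment that every randomised participant reaches has no stated place in the analysis. This is more than detail held back for an analysis plan, because the article positively fixes a two-level time factor that leaves the assessment out.

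Three things are at stake.

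- **The immediate effect.** The post-video score is the most direct evidence that the video moved planning, self-efficacy or intention, and it precedes attrition. Without a planned comparison, a null result at week 6 or 12 cannot be separated into a video that did nothing and one that worked and faded.
- **Carry-forward.** For a participant lost before week 6, the last psychological value on file is the one taken just after the video. Carrying it to weeks 6 and 12 treats an immediate reaction as a lasting effect.
- **Baseline.** Two scores are taken at the first visit and the article does not say which is the covariate. The post-video score comes after randomisation and after exposure, so adjusting for it would remove part of the effect against control.

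**Working it through.** **1. The plan's own figures (background only).** The article gives 66 at post-test, 35% loss and 102 recruited, with a large effect that is not given as a number. I assume Cohen's f = 0.40, three groups, a one-way F test, alpha 0.05 and noncentrality f² × N. Power is 0.798 at N = 63, 0.805 at 64 and 0.818 at 66. So 64 suffices, or 66 in three arms of 22. Then 66 / (1 − 0.35) = 101.5, rounded up to 102. Both figures reproduce, and nothing below changes them.

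**2. Occasions against models.**

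| Psychological occasion | Stated role in the MANCOVA |
|---|---|
| Before the video | baseline covariate, presumably; not stated |
| Straight after the video | none stated |
| Week 6 | outcome |
| Week 12 | outcome |

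One of the four occasions has no stated role. The mediation regressions could use it, but their mediator time point is not given.

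**3. Carry-forward.** The assumptions, none of them from the documents, are an immediate gain of 0.8 SD over control that has fully faded by week 6, correlation 0.5 between occasions, and the same loss in every arm. If a fraction p of participants contributes the post-video value in place of weeks 6 and 12, the expected spurious difference is p × 0.8 + (1 − p) × 0.

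- p = 0.20: 0.20 × 0.8 = 0.16 SD
- p = 0.35: 0.35 × 0.8 = 0.28 SD

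Simulation with N = 102 (68 in the two intervention arms against 34 controls, ANCOVA on the pre-video score) returns the same means. The true follow-up effect is zero, so rejection should be 0.05. It is about 0.14 to 0.15 at 20% loss. At 35% loss it is 0.28 to 0.35, the upper end when weeks 6 and 12 are averaged.

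The 35% is an upper bound. In the article it also covers missing data and spoilt questionnaires, and it is not specific to loss before week 6.

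**4. Post-video score as covariate.** Assume a lasting 0.8 SD effect, present in full straight after the video, and a slope of 0.5. The adjusted difference from control is 0.8 − 0.5 × 0.8 = 0.40 SD, half the true effect.

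**5. Information in the post-video comparison.** With up to 102 participants against 66, the standard error ratio is √(66/102) = 0.80. For an assumed 0.6 SD effect, two intervention arms pooled against control, noncentral-t power is 0.62 with 44 v 22 and 0.81 with 68 v 34. The 102 is a ceiling, because post-video questionnaires can be spoilt too. The pooled contrast is mine, not the plan's.

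**The case against.** A reader might infer that the post-video score enters no between-arm model at all and that a stated hypothesis is never tested. The documents do not support that.

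- The mediation regressions include a path from condition to each HAPA construct. That path is a between-arm contrast, and its time point is open. The imputation model could use the score as well. What can be said is that no model is stated to use it.
- The phrase "relative to the control condition from the time of intervention and at 6 and 12 weeks" can mean change counted from the start of the intervention. It covers all outcomes, including weight and lipids, which are not re-measured after the video. The abstract, the Design section and the mediator hypothesis name only the follow-up points. On that reading nothing goes untested.
- Not every scale is clearly measured twice at the first visit. Motivation is set at baseline, and action self-efficacy may have no true pre-video score.
- Carry-forward is an addition to multiple imputation, and the 0.6 SD, 0.8 SD, complete fade and 0.5 correlation are assumptions.
- For text against no text, both arms see the same video, so adjustment for the pre-video score is already unbiased. Using the post-video score would only add precision.

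All of this stands, and it narrows the point. Two things survive. Mediation is to be confirmed through indirect effects on biomedical outcomes, which is not a test of the immediate effect. And the carry-forward rule, as worded, does not exclude the post-video score.

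**Conclusion.** The point holds in a limited form. The post-video psychological scores are collected, but their role is not stated: the MANCOVA time factor excludes them, the mediator time point is open, and baseline is not defined for scales measured twice at the first visit. If the main hypothesis includes an immediate effect, no stated test addresses it.

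The carry-forward analysis, read literally, can overstate psychological effects at weeks 6 and 12 and so need not be conservative. The illustrative size is 0.16 SD at 20% loss and at most 0.28 SD at 35%, conditional on an immediate 0.8 SD gain that fades fully by week 6. A smaller gain, partial fading or less early loss gives less spurious effect.

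The consequences are confined to secondary psychological outcomes. Body weight is not re-measured after the video, so the primary outcome is untouched, and no sample-size figure changes. The change is still worth making, because it costs almost nothing and affects what the trial can say about mechanism.

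**What to change.** In Statistical analysis:

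1. Add a between-arm ANCOVA of each post-video HAPA score on condition, adjusted for the pre-video score where the scale has one, as the test of the immediate effect. If no immediate effect is hypothesised, reword the Hypotheses section to weeks 6 and 12 and state what the post-video score is for, for example as the mediator.
2. Define baseline for comparisons with control as the pre-video score. State that the post-video score is not carried forward as a week-6 or week-12 value.
3. Optionally, and for precision only, adjust the comparison of text with no text for the post-video score.

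For motivation and action self-efficacy, state whether both a pre-video and a post-video score exist.

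The cost is a few sentences and a few extra secondary tests, which should be labelled as such. No new data are needed.

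### Body weight, the primary outcome, is tested only inside a biomedical MANCOVA whose significance is the sole stated multiplicity control: this gives weak error control in that set and can block the primary test

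*Protocol article*

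**What the plan says.** The Statistical analysis section plans 3 (condition) × 2 (weeks 6 and 12) mixed-model MANCOVAs with baseline values as covariates: "A separate MANCOVA will be conducted for each set of dependent outcome variables: biomedical, behavioural and psychological". The next step is conditional: "Pending significant multivariate effects, follow-up univariate analysis of covariance (ANCOVAs) will be used to identify differences for individual variables" in each set. Post-hoc tests at the individual time points follow. No other multiplicity rule is written. An alpha appears only in the sample-size paragraph, "with statistical power set at > 0.80 and alpha set at" .05.

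The Abstract (Methods/Design) names body weight as the primary outcome and the rest as secondary. The Statistical analysis section does not single weight out, so as written it is one variable in the biomedical set.

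On the status of the other outcomes the wording is mixed. The Discussion says they will be explored. The Abstract, however, hypothesises statistical significance on primary and secondary outcomes alike, and the Hypotheses section says the text-message arm "will lead to statistically-significant independent improvements on the biomedical, psychological, and behavioural outcome measures, compared with the intervention and control conditions".

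**The concern.** A significant multivariate test protects the follow-up tests only when no variable in the set is affected. Once one variable truly responds, a significant MANCOVA says nothing about the others, yet each is then tested with no stated correction. The trial expects weight to respond, and BMI is weight over a fixed height squared, so it must respond too. Both sit in the same set as the lipids, glucose, insulin, blood pressure and waist-hip ratio. False claims of cardiovascular benefit then become more likely than a 0.05 threshold suggests.

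The gate also works in the other direction. If weight changes and little else does, the signal is spread over the whole biomedical set. The MANCOVA may then miss significance, and under the stated sequence the ANCOVA for the primary outcome is not reached.

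**Working it through.** **1. The plan's own figures.** The document calls the effect large without giving a number, and it does not name the G\*Power test. Assume f = 0.40 and a three-group univariate F test at 0.05. Noncentrality = N·f² = 66 × 0.16 = 10.56 on 2 and 63 df, giving power 0.818. N = 63 gives 0.798, so 66 is the smallest equal-arm total above 0.80. Dropout: 66 / (1 − 0.35) = 101.5, rounded up to 102. Both stated figures ("the total sample size required post-test is 66", and recruitment of 102) reproduce, and they do so with a test of a single variable.

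**2. Number of outcomes.** From the Abstract: 1 primary + 12 biomedical + 9 psychological + 2 behavioural = 24, so the biomedical set holds 13 including weight. Body fat percentage and muscle mass come from DEXA, which is not done at week 6, so 13 − 2 = 11 have both follow-ups.

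**3. No true effects anywhere.** Chance of at least one false multivariate result at 0.05 each:
- One treatment effect per set, 3 tests: 1 − 0.95³ = 14.3%.
- Condition and condition-by-time per set, 6 tests: 1 − 0.95⁶ = 26.5%.

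A simulation (22 per arm; sets of 13, 2 and 9; own-set baseline covariates; inter-outcome correlations 0, 0.3 and 0.6) gave 12.7%–13.3% and 24.4%–25.0%.

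**4. Weight truly changes.** Take d = 0.85 in both active arms. The group means 0, 0.85, 0.85 deviate from their average by −0.567, 0.283, 0.283, so f = √[(0.321 + 0.080 + 0.080)/3] = 0.40, the effect size in step 1. Every other biomedical outcome is null. A false claim means that the gate opens and at least one null outcome reaches p < 0.05.

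| Assumption | Gate opens | At least one false biomedical claim |
|---|---|---|
| Weight only affected, 12 null outcomes, baseline covariates, condition effect only, correlations 0–0.6 | 19%–45% | 13%–17% |
| Weight and BMI affected and nearly collinear (correlation 0.90–0.98), 8 null outcomes, weeks 6/12 correlated 0.7, condition and condition-by-time, other correlations 0–0.5 | 43%–78% | 24%–26% |
| As the row above, but weight and BMI no more correlated than any other pair | 79%–96% | 28%–34% |

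Counting only the condition effect in the second row gives 20%–24%. The first row leaves BMI unaffected, which cannot be so if weight changes. The third treats BMI as a largely separate signal, which it is not. The second row is the most plausible. The last two rows use a set of 10 variables and no covariates. The correlations are assumptions, since the document gives none.

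**5. Cost to the primary test.** Under the second row's assumptions, averaging weeks 6 and 12 gives variance (1 + 0.7)/2 = 0.85, so f = 0.401/√0.85 = 0.435. With N = 66, a direct test of weight then has about 88% power. The chance that the gate opens and weight is also significant is only about 42%–74%.

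**The case against.** The strongest reply has four parts.

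- **This is a condensed article.** Corrections for the ANCOVAs may be set out in an analysis plan not shown. That stands as far as a missing adjustment detail goes, and the point does not rest on one. The sequence of MANCOVA, then ANCOVA, is itself stated, it includes the primary outcome, and it gives only weak control whoever fills in the details.
- **One primary outcome is named, and the Discussion speaks of exploring the rest.** True, so it would be wrong to say that the outcomes are unranked. But the analysis does not use the ranking, and the Abstract and Hypotheses predict significance on the secondary outcomes.
- **The .05 is a sample-size input.** Also true. The document never promises 5% family-wise error over the secondary outcomes, so calling the rates above multiples of a stated guarantee would be unfair.
- **The gate often stays shut.** At the assumed effect size it opens in 19%–45% of trials with weight alone and 43%–78% with collinear BMI. This limits the false claims, but only by blocking the primary outcome as well.

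A reader might also infer that a real weight effect removes protection from all 24 outcomes, or that the false multivariate rate is simply about 25%. The documents support neither. A weight effect does not open the behavioural or psychological gates, and the upper figure needs two treatment effects tested per set.

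**Conclusion.** The point holds in a limited form. The written procedure gives weak error control and makes the primary analysis depend on a multivariate test of a much wider set.

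- With no true effects, the chance of at least one false multivariate finding is 14% to 26%, depending on whether one or two treatment effects are tested per set.
- With a true effect on weight at f = 0.40, the chance of at least one false biomedical claim is roughly 13% to 34%, most plausibly 24%–26%. The loss of protection is confined to the biomedical set and arises only when its gate opens.
- Under the same plausible assumptions, power for weight falls from about 88% to 42%–74%.

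The direction of these results does not depend on the assumed correlations, but the exact sizes do. They also rest on f = 0.40 for an effect described only as large, on 22 completers per arm, and on approximate set sizes.

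**What to change.** In the Statistical analysis section, test body weight by its own baseline-adjusted model at 0.05, outside the biomedical MANCOVA and not conditional on it. The sponsor should name in advance whether the test is at one time point or is an overall effect across weeks 6 and 12; the document hypothesises changes at both.

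Label all other biomedical, behavioural and psychological outcomes secondary and exploratory, and report them as adjusted differences with 95% confidence intervals. Align the Abstract and Hypotheses so that significance on these outcomes is not a confirmatory prediction. If the sponsor wants confirmatory secondary claims, it should choose a short list in advance and test it with a family-wise correction once the weight test has succeeded.

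This needs changes of wording only: no new data and no larger sample. The cost is weaker claims for the secondary outcomes; the gain is a primary test that the rest of the biomedical set cannot block.

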**Methods/Design:**

Overweight or obese participants will be randomly allocated to one of three conditions: (1) a psycho-education plus an implementation intentions and mental imagery condition; (2) a psycho-education plus an implementation intentions and mental imagery condition with text messages; or (3) a psycho-education control condition. The intervention will be delivered via video presentation to increase the intervention’s applicability in multiple contexts and keep costs low. We hypothesise that the intervention conditions will lead to statistically-significant changes in the primary and secondary outcome variables measured at 6 and 12 weeks post-intervention relative to the psycho-education control condition after controlling for baseline values. The primary outcome variable will be body weight and secondary outcome variables will be biomedical (body mass, body fat percentage, muscle mass, waist-hip circumference ratio, systolic and diastolic blood pressure, low-density lipoprotein, high-density lipoprotein, total cholesterol, triglycerides, blood glucose and insulin levels), psychological (quality of life, motivation, risk perception, outcome expectancy, intention, action self-efficacy, maintenance self-efficacy, goal setting and planning), and behavioural (self-reported diet intake, and physical activity involvement) measures. We also expect the intervention condition augmented with text messages to lead to statistically significant differences in the primary and secondary outcome variables at the follow up periods after controlling for baseline values.

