### Biomedical outcomes

Key outcome biomedical outcome measures will be taken to monitor changes in cardiovascular disease risk and body weight and composition as a result of the intervention [7,9,45]. All the biomedical outcome measures will be conducted at baseline, 6 and 12 week periods unless specified otherwise.

Within a three day period prior to the clinic appointment, blood lipoproteins including low-density lipoprotein (LDL), high-density lipoprotein (HDL), total cholesterol (TC), triglycerides (TG), and blood glucose and insulin levels will be taken at an approved pathology laboratory using a venous blood sample from each participants.

*Body weight (kg)* will be recorded with participants wearing light clothing and no shoes, using a digital body composition monitor scale (Omron, model HBF 362). *Height* (cm) will be measured at baseline, to the nearest 0.1 cm using a stadiometer with participants wearing light clothing and no shoes. *Body mass index* (BMI) will be calculated using both the weight and height measurements using the formula weight in kilograms divided by the square of the height in meters (kg/m^2^). *Waist-hip ratio* (cm) will be calculated by measuring waist circumference in standing position at the narrowest area between the iliac crest and lateral lower rib, and hip measurement from the largest circumference of the lower abdomen. This will be measured to the nearest 0.1 cm using a circumference measuring tape (Seca 203). To ensure greater accuracy the measure will be taken twice and the average of the two readings will be used.

*Systolic blood pressure* (SBP) and *diastolic blood pressure* (DBP) will be measured using an automated, blood pressure monitor (A & D Medical, model UA-851) with participants in a supine position with the tested arm at the level of their heart for at least a minimum of 10 minutes before and during measurements [46]. The measure will be taken three times and the average reading will be used. Body composition including *bone mass, body fat percentage,* and *muscle mass* will be measured using the whole body dual-energy X-ray absorptiometry (DEXA, Lunar Prodigy; Lunar, Madison, WI, USA). Participants will be required to lie on a bed during the DEXA scanning with no jewellery or metal clothing. DEXA scans will be performed at baseline and 12 weeks. The dual-energy X-ray absorptiometry machine will be calibrated and a phantom scan undertaken daily.

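### Body weight, the sole primary outcome, has no test of its own: it is reached only through a significant MANCOVA on the whole biomedical set, and the stated power does not allow for that gate.

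*Protocol article*

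**What the plan says.** The abstract (Methods/Design) fixes the hierarchy: "The primary outcome variable will be body weight and secondary outcome variables will be biomedical", followed by psychological and behavioural sets. Body weight is measured under Biomedical outcomes, whose opening sentence reads "Key outcome biomedical outcome measures will be taken to monitor changes in cardiovascular disease risk and body weight and composition". The mediation plan in Statistical analysis again classes the primary outcome as biomedical: "the primary and secondary biomedical outcome variables as the dependent variables".

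The same section sets the unit of testing: "A separate MANCOVA will be conducted for each set of dependent outcome variables: biomedical, behavioural and psychological". Baseline measures are covariates, and time (6 and 12 weeks) is a repeated factor. Individual variables come next, on a condition: "Pending significant multivariate effects, follow-up univariate analysis of covariance (ANCOVAs) will be used to identify differences for individual variables within each outcome set". Apart from the mediation regressions, which test indirect effects, no other analysis of body weight is described.

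The sample-size paragraph assumes a large effect (no number given), power above 0.80 and alpha 0.05. It arrives at 66 participants post-test and 102 recruited, allowing for 35% loss. It mentions neither the number of outcomes nor the multivariate step.

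**The concern.** A single primary outcome normally has a pre-specified test that stands by itself. Here the test of weight is conditional on a joint test that includes many secondary measures. A real difference in weight can go untested because blood pressure, lipids or insulin did not move enough to carry the joint statistic. The trial would then have no planned answer to its main hypothesis, and a weight test added after seeing the data would be post hoc. The stated power would also describe a procedure other than the one planned.

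The set contains a near-duplicate as well. Height is measured only at baseline, so for each participant BMI is weight divided by a constant. It takes up degrees of freedom and adds almost no information.

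**Working it through.** **1. Number of outcomes.** The abstract lists 12 secondary biomedical outcomes (reading body mass as BMI): "biomedical (body mass, body fat percentage, muscle mass, waist-hip circumference ratio, systolic and diastolic blood pressure, low-density lipoprotein, high-density lipoprotein, total cholesterol, triglycerides", then glucose and insulin. With weight that makes 13; bone mass, named under Biomedical outcomes, would make 14. But "DEXA scans will be performed at baseline and 12 weeks", so body fat and muscle mass have no 6-week value and cannot enter the 3 × 2 model. That leaves 13 − 2 = 11, or 10 without BMI.

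**2. Reproducing the stated sample size.** Inputs: three groups, alpha 0.05, one outcome. Assumptions: f = 0.40 for a large effect, and equal groups.

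- Noncentrality: λ = f²N = 0.40² × 66 = 10.56 on 2 and 63 df, giving power 0.818.
- The smallest N for 80% power is 64, or 66 with equal groups.
- Recruitment: 66 / (1 − 0.35) = 101.5, rounded up to 102.
- A repeated-measures between-group calculation (two visits, correlation 0.3, 0.5 or 0.7) gives 45, 51 or 57 and does not match.

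So 66 and 102 reproduce, but as a one-outcome test.

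**3. The gate.** With three groups, Wilks' lambda has an exact F. With p outcomes and c covariates, error df is ν = N − 3 − c, and F = [(1 − √Λ)/√Λ] × (ν − p + 1)/p on 2p and 2(ν − p + 1) df. For p = 13 and c = 0 that is 26 and 102 df, against 2 and 63 for weight alone.

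The effect pattern multiplies λ by a known factor. With common correlation ρ:

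- Other outcomes move only through their correlation with weight: factor 1, whatever the correlation.
- Only weight changes: [1 + (p − 2)ρ] / {(1 − ρ)[1 + (p − 1)ρ]}. For p = 13 this is 4.3/3.22 = 1.34 at ρ = 0.3 and 6.5/3.5 = 1.86 at ρ = 0.5.
- All change equally: p / [1 + (p − 1)ρ], which is 13/4.6 = 2.83 at ρ = 0.3 and 13/7 = 1.86 at ρ = 0.5.

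**4. Simulated results.** One visit, N = 66, f = 0.40 on weight, 13 outcomes, no covariate df removed (3000–5000 runs each):

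| Pattern | Gate opens | Gate opens and weight significant |
|---|---|---|
| Weight only, ρ = 0 | 0.28 | 0.27 |
| Four other body-size outcomes follow weight by correlation (0.6–0.9) | 0.28–0.29 | 0.27–0.28 |
| Weight only, ρ = 0.3 | 0.41 | 0.38 |
| Weight only, ρ = 0.5 | 0.56 | 0.51 |
| All equal, ρ = 0.3 | 0.80 | 0.68 |
| All equal, ρ = 0.5 | 0.59 | 0.54 |
| Several body outcomes, each with its own full effect | 0.97–1.00 | 0.81 |

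Direct ANCOVA on weight in the same runs: 0.81–0.82.

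**5. Sensitivity.**

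- *Ten outcomes:* weight only, 0.32–0.59.
- *Thirteen outcomes with 13 fitted baseline covariates:* 0.19–0.20 if the others follow by correlation, 0.21–0.38 if only weight changes, 0.38–0.56 if all change equally at ρ = 0.5 and 0.3. If four outcomes carry their own effect, the gate opens in 0.84–0.95 of trials.
- *All 102 analysed, weight only, ρ = 0, no covariate df removed:* the gate opens in 0.51 (13 outcomes) or 0.59 (10 outcomes), while direct power is about 0.95.
- *Completers for 80% gate power, same pattern:* about 160–168 (13 outcomes) or 144 (10 outcomes).

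**The case against.** **Membership of the set is inferred.** The Statistical analysis section never lists the biomedical variables, and the abstract applies the three labels to the secondary outcomes. This has some force. But only three sets exist, weight is measured under the biomedical heading, and the mediation sentence speaks of primary and secondary biomedical outcomes together. No other home for weight is described.

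**The loss may be much smaller.** The hypotheses expect improvement across the outcomes. If several outcomes carry their own full effects, little power is lost. That is right, and it is why a range is the honest answer. Even so, the plan states no such pattern, and power for the primary outcome should not rest on one.

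**The simulations use one visit.** The plan uses two. Combining them helps modestly: with 11 outcomes, one covariate and within-person correlation 0.7, the chance that the gate opens rises from 0.33 to about 0.39.

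Three stronger readings are tempting, and the document does not support them.

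- A reader might infer that the gate opens in only 20–22% of trials against 80–82% for a direct test. That pairs a 13-outcome, 13-covariate gate with a one-covariate ANCOVA under a near-worst pattern. The plan does not fix the number of covariates, and with the same 13 covariates the direct ANCOVA itself falls to about 0.72.
- A reader might infer that the trial was sized on weight. The sample-size paragraph never names it. What can be said is that the figure matches a one-outcome test.
- A reader might infer that movement in a secondary marker produces false weight findings. Weight must still pass its own ANCOVA, so the gate cannot raise its false-positive rate. The harm is lost power.

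**Conclusion.** The point holds. As written, the primary outcome is tested only after a significant joint test dominated by secondary outcomes, and the stated power above 0.80 does not carry over to weight under that procedure.

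At N = 66, direct ANCOVA power with baseline weight as the only covariate is about 0.81. Under the gate, across 10 to 13 outcomes and different covariate counts, the chance of reaching and detecting the weight effect is:

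- about 0.17–0.57 if only weight changes or the others follow by correlation, the low end with 13 outcomes and many covariates;
- about 0.4–0.65 if all outcomes change equally with moderate correlation (up to 0.71 in the most favourable run);
- nearly unreduced if several outcomes each carry their own full effect.

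These figures rest on f = 0.40, equal groups, Wilks' test and a single visit. The article supplies no correlations or effect pattern, so none of these values can be called the trial's actual power.

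**What to change.** - Take body weight out of the biomedical MANCOVA.
- Pre-specify an ungated primary analysis of weight at alpha 0.05: an ANCOVA or mixed model by condition, adjusted for baseline weight. Keep both the 6- and 12-week visits, since the hypotheses concern both.
- Keep the MANCOVA gate for the secondary biomedical outcomes only, and drop BMI as a separate dependent variable there.

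The cost is a change of wording in the analysis section, with no extra participants or data. The one downside is that weight no longer contributes to the secondary multivariate test.
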